### 2.11. Neuroimaging

Structural and functional images are acquired with 3T Siemens scanners with a 12-channel head coil at baseline, 14-week follow-up, and endpoint. T1-weighted images are obtained using a 3D magnetization prepared rapid acquisition gradient-echo (MPRAGE) sequence, setting slices = 192, field of view = 250 mm, thickness = 1 mm, flip angle = 9°, voxel size = 0.5 × 0.5 × 1 mm^3^, echo time = 2.44 ms, repetition time = 1900 ms, and inversion time = 900 ms for location purposes. Regarding resting functional MRI, we use the blood-oxygen-level-dependent (BOLD) signal to identify neural network changes carried out by iTBS related with motor and non-motor performance, with slices = 36, field of view = 192 mm, thickness = 3 mm, flip angle = 90°, voxel size = 3.0 × 3.0 × 3.0 mm^3^, echo time = 22 ms, repetition time = 2000 ms, and inversion time = 900 ms. Neuroimaging will be scanned at baseline, at the end of stage 1, and at the end of stage 2.

### 2.12. Electroencephalogram (EEG) and Electromyographic (EMG)

Resting EEG signals are received using EBneuro Beplus pro EEG 64-channel recording system (EBneuro, Florence, Italy) in a separate, quiet room. Sixty-four-channel EEG signals are sampled at a frequency of 1024 Hz, and a 50 Hz notch filter is applied to reduce the input noise. The individuals are instructed to seat comfortably in a stable chair with both hands relaxed during the recordings. The skin is cleaned at the electrode contacts with alcohol before attaching the 64-channel-customized EEG cap to reduce skin impedance. The distribution of the electrode gel is applied and adjusted with a flat syringe and cotton swab until all electrodes reach the desired impedance (<10 kΩ). Two sessions of resting EEG will be performed before and after the iTBS stimulus, which consist of 5 min of open eyes and 5 min of closed eyes. With 9 mm-diameter surface electrode patches, EMG traces will be acquired bilaterally from the abductor pollicis brevis (APB) muscles. EMG acquisition will be performed through the EMG module that affiliates to the iTBS stimulator. EEG and EMG measurements will be collected at baseline, week 2, midterm (week 14), week 16, and endpoint (week 28).

### 2.13. Blood Test

Peripheral blood will be collected at baseline, midterm (week 14), and endpoint (week 28). At the screening stage, 10 mL of peripheral blood will be drawn for routine laboratory tests, including blood cell sorting count, platelet count, hemoglobin level, liver and kidney function, blood creatinine, fasting glucose, and coagulation function tests. Peripheral blood will be drawn through a vein and collected into EDTA tubes. Within 30 min of collection, the supernatant is separated by centrifugation at 3000× *g* for 10 min at 4 °C to obtain plasma. The plasma is then packed into Eppendorf (EP) tubes of 0.5 mL each and stored at −80 °C for subsequent batch monitoring. Exosome alpha-synuclein (α-syn) will be measured using plasma. As a first step, antibody-coated superparamagnetic microbeads are used to isolate exosomes from human plasma [36]. Plasma samples are mixed with buffer A and buffer B and then diluted with phosphate-buffered saline (PBS), and the mixture is then incubated with dynabeads on a rotator at 4 °C for 1 h. Incubation of the mixture is continued with PBS on a rotator at 4 °C for 15 min and the supernatant containing plasma exosomes is collected. Plasma exosomes are characterized according to size and shape using transmission electron microscopy (TEM). The size of the sample is determined directly by nanoparticle tracking analysis (NTA) using a NanoSight LM10 microscope (Malvern Panalytical Ltd., [name]). The purity of positive and negative exosome markers is verified using Western blotting. Finally, the U-PLEX Human-Synuclein Kit (Meso Scale Discovery Co., Rockville, MD, USA) on the Quick Plex SQ120 platform is used to detect α-syn levels [37,38].

### 2.14. Baseline Assessments and Follow-Up Evaluations

After screening, all the eligible patients will undergo a comprehensive detailed assessment, including basic demographic, motor and non-motor symptoms, α-syn in the peripheral blood, and resting functional MRI, EEG, and EMG. All the physicians involved in assessment receive consistency training prior to the start of the trial to ensure the uniformity of the standard. Basic demographic information including gender, age, education, concomitant diseases, family history, medication usage, etc. is taken. All motor symptom assessments will be video-numbered and scored by two independent physicians. Various aspects of the patients’ clinical symptoms are measured using Unified Parkinson Disease Rating Scale (UPDRS), Berg Balance Scale (BBS), Hamilton Depression Scale (HAMD), Hamilton Anxiety Scale (HAMA), MMSE, Montreal Cognitive Assessment (MoCA), Pittsburgh sleep quality index (PSQI), 39-item PD Questionnaire (PDQ-39), 16-item odor identification test from Sniffin’ Sticks (SS-16), Scale for Outcomes in Parkinson’s disease for Autonomic Symptoms (SCOPA-AUT), and Wexner constipation scale. At the same time, we draw the patient’s peripheral blood for cytology, biochemistry, and coagulation tests and to detect α-syn in exosomes. After two intensive phases (week 2 and week 16), patients will receive a brief follow-up evaluation including the UPDRS, EMG acquisition and side effects. At midterm (week 14) and the endpoint of the experiment (week 28), the patients must complete the same detailed set of evaluations as the baseline.

### 2.15. Outcome Measures

According to the results of previous large delayed-start design disease-modifying drug studies, the neuroprotective effect can be commonly reflected by the difference in the changes in the UPDRS score before and after treatment between groups [22,39]. In an NET-PD study, the primary outcome is the differences in changes in UPDRS scores in the four groups before and after the iTBS intervention. As a secondary outcome, we will evaluate the effects of iTBS treatment on clinical symptoms, motor symptoms such as gaiting and postural balance, and non-motor symptoms such as mood, cognition, olfaction, and sleeping condition in PD patients. As a neuro-modulation intervention study, EEG, EMG and MRI images can also be visualized to indicate the functional activity status of the brain. The safety of the treatment will be assessed using a self-administered side effect scale. Additionally, self-administered side effects scales will be used to assess iTBS safety.

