### 2.2. Study Design

NET-PD is a 2-year prospective single-center, double-blind, multi-arm, delayed-start, sham-controlled trial. The study is conducted in two stages—the pseudo-controlled and active-treatment stage—with each stage consisting of a 2-week intensive phase and a 12-week maintenance phase, for a total of 14 weeks. The intensive period involves daily or twice-daily iTBS (or pseudo-stimuli) per week, for a total of 10 or 20 sessions, and the maintenance period consists of 12 weeks of iTBS (or pseudo-stimuli) once or twice a day, 2 days a week, for a total of 24 sessions in the single-stimulation group or 48 in the double group. In stage 1 (pseudo-controlled stage), patients are randomly assigned to one of four intervention groups in a 1:1:1:1 ratio: early-start single iTBS group (A1), early-start double iTBS group (A2), delayed-start single iTBS group (S1), and delayed-start double iTBS group (S2). The early-start groups conduct active iTBS throughout, whereas the delayed-start groups use pseudo-stimuli in the first stage and start using iTBS in the second stage. The only difference between the single- and double-stimulation group is the number of sessions per day: once daily for the single group and twice daily for the double group. In stage 2 (active treatment stage), participants in A1 and A2 continue to receive the same iTBS protocol as the first stage, while those in S1 and S2 start to receive active iTBS. All patients are required to have a detailed follow-up clinical assessment and electrophysiology record at baseline, 2 weeks, 14 weeks, 16 weeks, and 28 weeks. MRI and peripheral blood are collected at baseline, 14 weeks, and 28 weeks (Figure 1, Table 1). Each patient will spend 7 months in this study and the total duration of the research will be approximately 2 years, from July 2022 (first in) to December 2024 (last out) (Figure 2).

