### 2.17. Sample Size and Statistical Analysis

With reference to data from previous studies published in relevant journals, a total of 60 PD patients are proposed to be enrolled in this single center study. The sample size of this study was calculated based on the improvement in the UPDRS scale after 28 weeks of treatment and differences between groups. Calculations are performed using PASS (Power Analysis and Sample Size) 2008 software (UT, OH, USA), assuming a four-point reduction in the UPDRS at the end of treatment in A1, a five-point reduction in A2, a two-point reduction in S1, and a four-point reduction in S2, with a standard deviation of 2, a test level of 0.05, and a degree of certainty of 0.9 yielded for 13 subjects per group. Considering that the patient dropout rate may be about 10% [24,40], the final plan is to enroll n = 15 cases in each group for n = 60 cases in total. The minimum sample size required to meet the hypothesis of this clinical study is 60, and actual samples of 60 cases or more are in accordance with the clinical study design principles and statistical requirements.

Statistical analysis applies SPSS 20.0 for processing; MRI, EEG, and EMG data are processed on MATLAB platform (Math Works Inc., Natick, MA, USA). All statistics are performed using two-sided tests, and α = 0.05 is the cut-off point used to decide whether the hypothesis is statistically significant. Between-group comparisons of quantitative data will be performed using analysis of variance (ANOVA) or Wilcoxon rank sum test depending on the distribution of the data. A paired *t*-test or Wilcoxon signed-rank test will be used for comparison before and after treatment. Categorical data are tested by chi-square test or exact probability method (if the chi-square test is not applicable).

To compare the changes in UPDRS scores before and after the iTBS intervention at each time point, mainly comparing the differences in their means, two-way repeated-measures ANOVA was used to compare the main effects and the interaction effects between the two for different groups and follow-up points (baseline, week 14, week 28), and post hoc analysis was performed using the Bonferroni test to compare the differences between each follow-up point and baseline scores.

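### The side effect scale has no baseline administration, so if it records general symptoms, complaints already present cannot be told from new ones within patients, chiefly in A1 and A2

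*Protocol article*

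**What the plan says.** Section 2.15 (Outcome Measures) names one safety outcome: "The safety of the treatment will be assessed using a self-administered side effect scale". It gives neither the items of the scale nor a rule for attributing a complaint to treatment.

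The side effects row of Table 1 is marked at weeks 2, 14, 16 and 28. Its screening and baseline cells are empty. Section 2.14 does not name the scale in the baseline battery. For weeks 2 and 16 it says "patients will receive a brief follow-up evaluation including the UPDRS, EMG acquisition and side effects", and for weeks 14 and 28 that "the patients must complete the same detailed set of evaluations as the baseline".

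On control, Section 2.2 says that "the delayed-start groups use pseudo-stimuli in the first stage and start using iTBS in the second stage". In stage 2, A1 and A2 continue active treatment "while those in S1 and S2 start to receive active iTBS", so all four arms are then active. On numbers, Section 2.17 says "the final plan is to enroll n = 15 cases in each group for n = 60 cases in total".

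**The concern.** The Introduction lists sleep, autonomic and psychiatric disturbances among the non-motor features of Parkinson's disease, and Section 2.3 admits patients aged 50 to 80 up to Hoehn–Yahr stage 4. Many may therefore bring complaints to the first session that a general symptom checklist would record. Without a score from before stimulation, this scale cannot show whether a complaint at week 2 or later is new, worse or unchanged. The before-and-after paired tests that Section 2.17 foresees in general terms have no before value to use here.

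At stake is how the raw side effect rates are read. The gap is widest in A1 and A2, half of the trial. Their first score comes after two weeks of active iTBS, and in stage 2 they have no concurrent sham group. A missed pre-treatment score cannot be recovered later.

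**Working it through.** **Plan's own figures.** The plan gives no figure for side effects. Its group size does reproduce. A one-way ANOVA with reductions of 4, 5, 2 and 4, SD 2 and alpha 0.05 has power 0.872 at 12 per group and 0.901 at 13. Then 13/(1 − 0.10) = 14.4, rounded up to 15 per arm. Stage 1 therefore compares 30 active with 30 sham patients.

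**Which score can serve as a reference (Table 1 against Section 2.2).**

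| Arms | Stage 1 | Stage 2 | Score on this scale before active iTBS |
|---|---|---|---|
| A1, A2 | active, with concurrent sham arms | active, no concurrent sham | none |
| S1, S2 | sham | active, no concurrent sham | weeks 2 and 14, under sham |

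**Effect on rates.** The values below are assumptions; none is in the documents. Let b be the share of patients with a complaint before treatment that the scale would record, and t the true incidence among the rest.

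- Raw active rate = b + (1 − b)t
- Sham rate = b
- Active minus sham = (1 − b)t

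With t = 0.10:

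| b | Raw active | Sham | Difference |
|---|---|---|---|
| 0 | 0.10 | 0 | 0.10 |
| 0.1 | 0.19 | 0.10 | 0.09 |
| 0.3 | 0.37 | 0.30 | 0.07 |
| 0.5 | 0.55 | 0.50 | 0.05 |

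With t = 0 the difference is 0 at every b. The raw rate is inflated, but the stage 1 contrast does not credit existing complaints to iTBS. In S1 and S2 the same subtraction works from week 14 to weeks 16 and 28, apart from changes over time. In A1 and A2 there is nothing to subtract within patients. With a baseline score, the incidence among those free of the complaint is recovered: (0.37 − 0.30)/(1 − 0.30) = 0.10.

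**Chance imbalance in stage 1.** The 95% range of a difference in baseline prevalence between two groups of 30 is 1.96 × √(2b(1 − b)/30):

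- b = 0.2: ±0.202
- b = 0.3: ±0.232
- b = 0.5: ±0.253

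This is the ordinary sampling variation of a 30 versus 30 comparison. The chi-square or exact tests in Section 2.17 already allow for it. A baseline score could reduce it; leaving the score out adds no bias.

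**The case against.** The strongest reply is that the scale may ask only about effects of the stimulation. It would then have little meaning before the first session, and starting at week 2 would be natural. Its wording is not shown, and an article commonly leaves such detail to the full protocol. This stands, and it makes the point conditional. A reader might infer that existing Parkinson's symptoms will be counted as iTBS side effects; the documents do not support that.

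A reader might also infer that stage 2 has no control of any kind. That is too strong. It has no concurrent sham group, but S1 and S2 carry their week 14 score under sham into it. For A1 and A2 the reply gives no help.

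Other measures cover part of the ground. PSQI, HAMD, HAMA, SCOPA-AUT, Wexner, PDQ-39 and UPDRS are taken at baseline and again at weeks 14 and 28, so worsening of sleep, mood and autonomic complaints can be followed there. Section 2.14 includes blood tests, Section 2.5 makes an intolerable adverse event a ground for withdrawal, and the Discussion describes monthly meetings that cover patient safety. All of this stands, but another instrument cannot supply a change score on the side effect scale.

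Lastly, Section 2.14 and Table 1 might be read as contradicting each other on weeks 14 and 28. They do not: repeating the baseline set does not rule out a further form, and Table 1 adds one.

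**Conclusion.** The point holds as a minor, conditional weakness of a fixed visit schedule. The only named safety outcome has no pre-treatment score. If the scale records general symptoms, raw rates on it cannot be read as caused by iTBS, and change within patients cannot be obtained for A1 and A2 in either stage.

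The size depends on the unknown prevalence of existing complaints. At an assumed true incidence of 10%, the raw rate runs from 19% to 55% as that prevalence goes from 10% to 50%.

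The stage 1 active-versus-sham comparison is unbiased, because randomisation balances existing complaints in expectation; it only forgoes some precision. The ±20 to ±25 points of chance imbalance should not be taken as the size of an error. For S1 and S2, week 14 is a usable reference, provided the form is completed before the first active session and changes over time are kept in mind.

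**What to change.** Add a baseline mark to the side effects row of Table 1 and name the scale in the baseline list of Section 2.14, to be completed before the first session. Report items new or worse than baseline, by arm and stage. For S1 and S2 in stage 2, also report items new or worse than week 14.

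For A1 and A2, keep baseline as the reference in both stages. Their week 14 score follows 14 weeks of active iTBS, so using it as the reference would hide effects that began in stage 1 and persisted.

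The cost is one more self-completed form at a visit that already takes place, a few minutes of patient time. Patients enrolled before the change would have no baseline score and should be identified as such in the report.

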### 2.5. Withdrawal Criteria

Subjects may withdraw at any time if anything occurs that may jeopardize their interests. Subjects who discontinue the study will no longer be covered by continued data collection. The reason for termination or withdrawal should be documented in the case report form. Patients should withdraw from the trial immediately if they meet the following criteria:Poor compliance to the protocol;Occurrence of an intolerable adverse event;Patients decline further treatment or follow-up;Loss of visits due to unavoidable situations, such as death;The investigators terminate the subject’s continued participation after review.

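### Side effect data stop when a patient withdraws for an intolerable adverse event, so a scale-based safety result can under-count the harms that force patients out

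*Protocol article*

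**What the plan says.** Section 2.15 of the protocol article gives one safety measure: "The safety of the treatment will be assessed using a self-administered side effect scale". The sentence after it repeats this, and no other safety outcome is named. Table 1 places side effects at weeks 2, 14, 16 and 28; section 2.14 confirms weeks 2 and 16.

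Section 2.5 lists grounds for leaving, introduced by "Patients should withdraw from the trial immediately if they meet the following criteria". One of them is "Occurrence of an intolerable adverse event". The same section states "Subjects who discontinue the study will no longer be covered by continued data collection", with no exception for safety. What it does ask for at that point is the reason: "The reason for termination or withdrawal should be documented in the case report form". Section 2.6 counts a patient who withdraws midway as having completed the experiment and describes no exit assessment.

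On the design, section 2.2 says that "the delayed-start groups use pseudo-stimuli in the first stage and start using iTBS in the second stage". Stage 1 is therefore the only period with a sham comparison.

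**The concern.** Each rule is ordinary on its own, but together they make the safety measure depend on the outcome. An event bad enough to be intolerable ends participation at once, ending participation ends data collection, and the scale is taken only at scheduled visits. Patients who tolerate treatment supply all four scales; those who do not supply only the ones completed before the event. A side-effect rate computed from the scale would then miss the events that drove patients out.

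Stage 1 is where this matters most. Once the delayed-start arms switch to active iTBS, no later data can replace a lost sham-controlled comparison. The trial also sets once-daily against twice-daily stimulation, so tolerability by arm bears on the choice of regimen.

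**Working it through.** **Inputs.** From section 2.17: 13 patients per group before dropout, 15 per group and 60 in total after it, and this dropout expectation: "Considering that the patient dropout rate may be about 10" per cent. From Table 1: side effects at weeks 2, 14, 16 and 28. The article does not say what share of dropouts would be due to adverse events, so that share is an assumption below.

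**The plan's own figure.** 13 / (1 − 0.10) = 14.4, rounded up to 15 per group; 4 × 15 = 60. This reproduces. The point does not depend on the power calculation.

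**What each patient contributes if the rules are followed.**

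| Time of withdrawal for an adverse event | Scales completed | Is the event on a scale? |
|---|---|---|
| Week 1 | none | no |
| Week 8 | week 2 | no, that scale precedes the event |
| Week 15 | weeks 2 and 14 | no |
| Week 20 | weeks 2, 14 and 16 | no |

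The gap between scales is 12 weeks in each maintenance phase (weeks 2 to 14 and 16 to 28).

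**How many patients.** Expected dropouts: 0.10 × 60 = 6. If k of these leave for an adverse event between scheduled scales, the share of patients whose event no scale records is k/60:

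| k (assumed) | k/60 |
|---|---|
| 0 | 0% |
| 2 | 3.3% |
| 4 | 6.7% |
| 6 | 10.0% |

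The 10% is a planning figure and not a ceiling.

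**Effect of one patient on a side-effect rate.** If the patient reported nothing on an earlier scale and stays in the denominator, the rate falls short by 1/15 = 6.7 percentage points in one arm, 1/30 = 3.3 points in A1 and A2 combined, and 1/60 = 1.7 points overall. If the patient reported a side effect earlier, a rate of any side effect does not move, but the severity of the later event is still missing.

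**Effect on the stage 1 contrast.** With a such patients in the active arms (A1 + A2, 30 patients) and s in the sham arms (S1 + S2, 30 patients), the active-minus-sham difference is understated by (a − s)/30. For a = 2 and s = 0 this is 6.7 points; for a = s it is zero. The rate within each group is under-counted in any case. The contrast favours active iTBS only if such withdrawals are more frequent under active stimulation.

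**The case against.** The best counter-argument is that the sentence ending data collection may only rule out continued follow-up, and need not forbid a form at the withdrawal contact itself. A condensed article would leave exit visits and adverse event reporting to the full protocol. Section 2.15 names an instrument; it does not say that safety will be reported from the scale alone. Withdrawals for adverse events can already be counted by arm from the case report form. Other contact exists too: maintenance sessions take place "once or twice a day, 2 days a week", and section 4 provides for monthly discussion of patient safety. Section 2.9 reports that iTBS was well tolerated in earlier work, so the number affected may be nil.

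Much of this stands as a limit on size. The event is known, fuller recording may exist elsewhere, and no count can be derived from the article.

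It does not remove the point. The article states the stop in data collection as a rule with no exception for safety, so this is more than silence. The other records are not made part of the safety outcome in section 2.15. Having the reason for withdrawal on file does not supply the scale, nor does it say that the two will be reported together.

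**Conclusion.** The point holds in its limited form. As the article is written, a patient withdrawn for an intolerable adverse event gives no later side effect scale, so a safety result built on the scale can under-count these events. The size is unknown: 0% to 10% of the 60 patients if 0 to 6 of the expected 6 dropouts leave for this reason, and up to 6.7 percentage points per patient in one arm. This assumes that the withdrawal rules are followed literally, that the event falls between scheduled scales, and that the result rests on the scale alone. A bias in favour of active iTBS also needs more such withdrawals in the active arms than in the sham arms during stage 1. The primary UPDRS analysis, the sample size and the power are not affected. This is a worthwhile, inexpensive improvement rather than a threat to the trial's main result.

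**What to change.** Two sentences would do.

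- **Section 2.5:** exempt safety from the stop in data collection, so that a patient who withdraws completes the side effect scale at that time where possible.
- **Section 2.15:** state that withdrawals for an adverse event, as recorded in the case report form, are reported by arm together with the scale results, with stage 1 shown separately. This uses information section 2.5 already requires, so it also covers patients who decline the exit scale.

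The cost is one extra form at withdrawal and no extra scheduled visits. The side-effect rate may come out slightly less favourable.
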